## Abstract

**Background:**

Intimate partner violence (IPV) is described by the American Medical Association as "a pattern of coercive behaviors that may include repeated battering and injury, psychological abuse, sexual assault, progressive social isolation, deprivation, and intimidation." The long-term consequences of IPV include health risks, posttraumatic stress disorder, depression, and staggering economic costs for health care of victims. Intimate partner violence is often underreported among women who seek medical attention. The current study seeks to address the issue of possible underreporting of IPV in orthopaedic fracture clinics by establishing prevalence rates of IPV among women seeking treatment for musculoskeletal injuries.

**Methods/Design:**

We propose a cross-sectional multicenter study wherein 3,600 women will complete a self-reported written questionnaire across clinical sites in North America, Europe, and Australia. Recruitment of participants will take place at orthopaedic fracture clinics at each clinical site. The questionnaire will contain a validated set of questions used to screen for IPV, as well as questions that pertain to the participant's demographic, injury characteristics, and experiences with health care utilization. Female patients presenting to the orthopaedic fracture clinics will complete two validated self-reported written questionnaires (Woman Abuse Screening Tool (WAST) and the Partner Violence Screen (PVS)) to determine the prevalence of IPV in the past 12 months and in their lifetime. The two questionnaires were designed for rapid assessment of IPV status in emergency departments, family practice, and women's health clinics that we believe are similar to our intended setting of an orthopaedic clinic.

**Discussion:**

If the prevalence of IPV among women attending orthopaedic clinics is greater than the current perceptions of orthopaedic surgeons, this study will serve to advocate for the continued education of medical professionals to better recognize probable IPV cases and offer existing services to enhance the care of these patients.

## Background

Intimate partner violence (IPV) is described by the American Medical Association as "a pattern of coercive behaviors that may include repeated battering and injury, psychological abuse, sexual assault, progressive social isolation, deprivation, and intimidation" [1]. The long-term consequences of IPV include health risks, posttraumatic stress disorder, depression, and staggering economic costs for health care of victims [2].

The cumulative lifetime prevalence of domestic violence for women admitted to the Emergency Department is approximately 54 percent [2]. However, IPV is underreported among women who seek medical attention [2-4]. The American College of Surgeons position statement on IPV states that surgeons have the responsibility to identify IPV and appropriately treat women at risk of further harm [5]. In July 2009, the Canadian Orthopaedic Association (COA) released a position on the role of the orthopaedic surgeon in the care of abused women. The statement affirms that the "COA recognizes that IPV is a significant social determinant of morbidity and mortality, and that orthopaedic surgeons are well positioned to identify patients living with IPV and initiate an intervention. Therefore, the COA encourages its members to educate themselves further about IPV and considers it good medical practice to take steps to identify and offer assistance to its victims" [6]. In accordance with this position statement, the COA is working towards raising awareness of domestic violence as well as educating orthopaedic surgeons over the next year. This shows the timeliness of the issue in orthopaedic surgery.

Despite these positive initiatives, there is currently no data in orthopaedic literature to support the hypothesis that the prevalence of IPV in orthopaedic trauma clinics warrants additional resources to identify and manage victims [7,8]. The current study seeks to address the concern that IPV is underreported in orthopaedic fracture clinics by establishing prevalence rates of IPV among women seeking treatment for musculoskeletal injuries across multiple centers in different jurisdictions. This will be the first multi-center study to evaluate this critical issue in the field of orthopaedic trauma.

The proportion of women in Canada 15 years of age and older who have experienced physical or sexual violence in a marital or common-law union in the last 5 years is between 6 percent and 8 percent, affecting approximately 300,000 women in the province of Ontario [9]. This is likely an underreporting of the true rate since detection is hindered by the reluctance of respondents to talk openly about their IPV experience [10]. In documented cases of IPV in Canada, 25 percent of women reported that they were beaten, 20 percent reported choking, and 20 percent were sexually assaulted. Of the documented cases, 40 percent of women in Canada who have experienced IPV suffer a physical injury, and 15 percent of these cases are serious enough to warrant medical attention [10].

Several studies have found that IPV is underreported among women who seek medical attention [2-4]. Dearwater et al. noted that women who were treated at 11 community hospital emergency departments secondary to IPV-related acute trauma were identified in only 44 percent of all cases presented [3]. Davis et al. reported that of the victims who presented to a level I trauma center because of confirmed or probable IPV, only 26 percent received referrals to social services and 63 percent were discharged without any investigation into their safety at home [11]. The investigators further note that the number of IPV victims was underestimated because of the propensity of conflicting information in the patients' history, lack of information to adequately rule out IPV, and failing to actively screen for IPV among all cases who presented to their trauma service. Additionally, a recent study found that sprains, dislocations, fractures, and foot injuries accounted for 28 percent of all clinical manifestations of IPV among women who were identified in a 2-year period by the Minnesota Domestic Abuse Program [12]. Despite these findings, IPV remains underemphasized in this medical field [7].

The majority of orthopaedic surgeons (87%), however, in a Canada-wide survey believed that female victims of IPV accounted for less than 1 percent of patients in their care [7]. The findings of this survey suggested a misperception between surgeons' beliefs about the prevalence of IPV in their fracture clinics and reported rates of IPV in the community [7]. Current guidelines suggest that orthopaedic surgeons should play an active role in the identification of IPV victims and their timely referral to local agencies [7,13,14].

To explore prevalence rates of IPV in the fracture clinic setting, we conducted a pilot screening study of injured women across two trauma centers in Ontario. We found that one third of women have been victims of IPV (including physical, emotional, and sexual abuse) in the past 12 months. Furthermore, we found that 2.5 percent of women presented with injuries directly resulting from IPV [15]. While our findings were compelling, the generalizability between two level I trauma centers remained unknown. The current proposal aims to expand the generalizability and significantly increase the sample size to provide more precise estimates of IPV in the fracture clinic setting.

### Research Objectives and Hypotheses

The primary objective of this observational study is to determine the proportion of women who have experienced IPV in the past 12-months among women who present to orthopaedic fracture clinics for treatment of orthopaedic injuries. We define IPV as physical, emotional, or sexual abuse that is caused by an intimate partner such as a victim's spouse, common-law partner, or dating partner.

Secondary objectives include determining the proportion of women presenting to orthopaedic fracture clinics for the treatment of orthopaedic injuries who have experienced IPV in their lifetime; determining the proportion of women who present to orthopaedic clinics for treatment of orthopaedic injuries that present with an orthopaedic injury that was the direct result from IPV from a current and ongoing relationship; and investigating patients' previous experiences, knowledge, and perceptions with regards to approaching healthcare professionals about IPV.

We hypothesize that the prevalence of IPV among women who present to orthopaedic fracture clinics for treatment of orthopaedic injuries is sufficiently high to warrant targeted programs to assist orthopaedic surgeons in the clinic with identification and appropriate referral to specialists.

## Methods/Design

We propose a cross-sectional multi-center study wherein 3,600 women will complete a validated self-reported written questionnaire across ten clinical sites in North America, Europe, and Australia. Recruitment of participants will take place at the fracture clinic at each clinical site. The questionnaires will contain a validated set of questions used to screen for IPV, as well as questions that pertain to the participant's demographic, fracture characteristics, and experiences with health care utilization. A flow diagram of the study is presented in Figure 1.

**Figure 1 F1:**
[figure not shown]
**Study Flow diagram**.

### Rationale for an Observational Study Design

We explored the possibility of addressing our research questions by other less costly or less time-consuming study designs. Other methods considered were a retrospective cohort and a cross-sectional study using a self-reported written questionnaire sent by mail. The advantages and disadvantages of these study designs when compared to the proposed design are discussed below.

A retrospective cohort study would be less costly and time consuming than the prospective cohort study or case-control study proposed. A medical chart review can be undertaken at each participating clinic, where data collectors can review the charts for reported cases of IPV among patients who visited the clinic within a certain time period. Such a study would have a greater likelihood of undergoing an expedited ethics review than a study that requires active participation from the respondent. However, given that IPV is not properly recognized among health professionals [3,4,16], such a review would likely be unable to detect a significant proportion of IPV victims. Moreover, the non-standardization of the definition of IPV may also affect the internal validity of the study and result in an over reporting or underreporting of cases of IPV.

The use of a mailed questionnaire that can be completed and sent back by the participant is a potential strategy that would save costs over a study that requires the respondent to be present at the clinic to be enrolled. Female patients over the age of 18 years can be identified from the registries of the orthopaedic fracture and injury clinics and be mailed a written questionnaire and information letter about the study. Informed consent would be implied if the questionnaire is sent back to the study investigators. However, while such a study would be easier to implement than a prospective study, the administration of a mailed questionnaire has been met with limited success. In their study of abuse prevalence among patients visiting gynaecology clinics, Wijma et al. noted response rates as low as 67 percent among recruiting clinics that mailed questionnaires to eligible participants [4]. Campbell et al., in their attempt to assess the physical consequences of IPV with a questionnaire that was mailed, reported a response rate of only 12 percent [17].

In contrast to the use of mailed questionnaires, written self-reported surveys such as the questionnaire suggested in the proposed study design may have less likelihood of response bias. Use of such questionnaires has resulted in response rates between 62 percent and 95 percent among women who are invited into the study personally by research personnel and then administered the questionnaire if they chose to participate [1,4,18,19].

### Inclusion and Exclusion Criteria

All women who present to a recruiting orthopaedic or trauma clinic will be screened for eligibility. Our inclusion criteria for this observational study are: 1) The patient presents to the fracture clinic for her own appointment; 2) The patient is 16 or 18 years of age or older; 3) The patient is able to read and write well enough to complete the study questionnaires; 4) The patient is being seen at the fracture clinic for the treatment of an orthopaedic injury; and 5) The patient is able to separate herself from anyone who accompanied her to the fracture clinic to complete the questionnaire in privacy. Clinical sites may include patients who are over the age of 16 years in the study if it is permitted by their Research Ethics Board. Some sites may not allow patients under the age of 18 to participate. Lowering the age requirement to 16, where possible, will improve the generalizability of the study and will allow us to determine the rates of IPV in a younger demographic.

The exclusion criteria for this study are: 1) The patient is considered too ill or injured to participate in the study; and 2) The patient is cognitively impaired and unable to participate in the study.

Similar inclusion and exclusion criteria have been used in other studies that sought women's experience with IPV [1,3,8,16]. Once a patient is deemed eligible, she will be invited to participate in the study by a female study coordinator. We will track the number of patients screened and their reasons for ineligibility.

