Another research question that will be addressed in the study is what are patients' previous experiences and perceptions about discussing IPV with health care professionals. To that end, the questionnaire will also query the participant about her age, income, education, race/ethnicity, marital status, sexual orientation, and length of relationship. Additionally, participants will be queried about perceptions and previous experiences with reporting IPV in health care settings.

The questionnaire will also ask participants to record the characteristics of the injury that they are being seen for in the fracture clinic including: type of injury, how the injury occurred, locations of injury, and date of injury.

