Justice and inclusiveness are respected by including all individuals who present to the orthopaedic fracture clinic that are relevant to the research question. Age restrictions are in place in light of possible legislative requirements within the geographic areas of the recruiting clinics, and exclusion criteria have been minimized to only those individuals who have a high likelihood of providing poor quality data or being unable to properly provide free and informed consent, given that the questionnaire is available only in the primary language of each participating site (i.e. English in Canada and the United States and Dutch in the Netherlands).

Harm will be minimized by respecting the participant's privacy and affirming to her that the care she receives is in no way affected by her decision to participate or not participate in the study. In addition, Dearwater et al. noted in their study that as a safety precaution women were only administered their questionnaire while in the absence of any friends, family, or medical staff [3]. We will adopt these criteria for our study as well.

To maximize benefit, individuals who are approached to participate in the study will be offered information resources pertaining to IPV and contact information of local IPV services in the clinic area. Fracture clinic staff will also be aware of the study and will also be provided with these materials in the event that the individual approached would prefer to speak to her care provider(s) about IPV instead of members of the study team.

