### Data Analysis

Data will be analyzed using SPSS Version 17.0 [SPSS, Chicago, IL] and will be stratified according to clinical center, at which point descriptive statistics can be reported for each site and overall. Dichotomous data will be reported as number of participants and proportions, with corresponding confidence intervals to estimate precision. Continuous data will be presented as means and medians with standard deviations. We will provide descriptive statistics describing the patient demographics and injury characteristics across each clinical site. We will also report the results of the WAST and PVS across each clinical site for IPV prevalence in the past 12 months. These two screening tools will be scored according to the developers guidelines. Finally, we will report descriptive statistics, with 95% confidence intervals, across each clinical site on patient's previous experiences, knowledge, and perceptions with regards to approaching health care professionals about IPV. We will use Chi-square tests (dichotomous variables) or t-tests (continuous data) to determine if there are differences in IPV prevalence across different clinical sites and jurisdictions.

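### The minimum age may be 16 or 18 depending on the site, but prevalence is compared across sites and jurisdictions with no common age range, so part of a difference between sites with different age floors may come from the eligibility rule

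*Protocol article*

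**What the plan says.** Under Inclusion and Exclusion Criteria, the Protocol article gives the age criterion as "The patient is 16 or 18 years of age or older". A site may use the lower limit "if it is permitted by their Research Ethics Board", and the article adds: "Some sites may not allow patients under the age of 18 to participate". The reason given for going down to 16 is generalizability, and that it "will allow us to determine the rates of IPV in a younger demographic".

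Under Ethical Considerations the age limit is linked to place: "Age restrictions are in place in light of possible legislative requirements within the geographic areas of the recruiting clinics".

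Under Data Analysis, the data "will be stratified according to clinical center", and chi-square tests or t-tests are used "to determine if there are differences in IPV prevalence across different clinical sites and jurisdictions". No age range, age stratum or age adjustment is named for these tests.

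Age is collected. Under Primary and Secondary Outcome Measures, "the questionnaire will also query the participant about her age". The section on protecting against bias does not list the mixed age floor.

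**The concern.** The age floor is decided by ethics board and linked to local legislation, so it can follow the same boundaries as the jurisdictions being compared. If one side enrols 16-17-year-olds and the other does not, eligibility is confounded with the comparison. An apparent difference could then arise, or a real one be hidden, for a reason unrelated to how common IPV is among comparable patients.

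The direction need not be the same for every outcome. Lifetime IPV accumulates with years of exposure, so including the youngest women could lower it, while 12-month IPV could move either way. Stratifying by center does not help, because the floor is constant within a center.

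**Working it through.** **The plan's own figure.** The Sample Size section gives n = 278 at 5% prevalence with a 95% interval of 2.78% to 8.31%. The exact (Clopper-Pearson) interval for 14/278 is 2.78% to 8.31%, which matches. The total also agrees: 12 × 300 = 3,600. Neither figure depends on the age floor, so the sample size is not in question.

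**Inputs from the documents.** 300 women per site, 12 sites, planning prevalence 5% (Sample Size); pilot 12-month prevalence of one third (Ontario PRAISE Pilot Study).

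**Assumptions, not in the documents.** The share f of enrolled women aged 16-17 at sites that admit them: mid value 5%, range 1% to 10%. Their IPV rate divided by that of women 18 and over, R: mid value 2, range 0 to 3. Six sites on each floor, and no true difference between sites among women 18 and over.

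**Formula.** A site with a floor of 16 has expected prevalence (1 − f) × p + f × R × p, where p is the prevalence at 18 and over. The shift due to the age rule is f × (R − 1) × p.

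- At p = 5%: 0.05 × (2 − 1) × 5 = 0.25 points.
- At p = 33.3%: 0.05 × (2 − 1) × 33.3 = 1.67 points.

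**Against random error.** The half-width for one site is 1.96 × √(p(1 − p)/300). For a difference between two groups of n women it is 1.96 × √(2 × p̄(1 − p̄)/n), where p̄ is the mean of the two prevalences (5.125% and 34.17%).

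| Mid case (f = 5%, R = 2) | p = 5% | p = one third |
|---|---|---|
| Shift (points) | 0.25 | 1.67 |
| Half-width, one site of 300 | 2.5 | 5.3 |
| Half-width, difference 300 v 300 | 3.5 | 7.6 |
| Half-width, difference 1,800 v 1,800 | 1.4 | 3.1 |
| Rejection, 300 v 300 | 5.2% | 7.1% |
| Rejection, 6 v 6 sites | 6.3% | 18.4% |
| Rejection, 12-site chi-square (11 df) | 5.3% | 8.4% |

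The nominal rejection rate is 5%. For the 6 v 6 comparison at one third, the standard error is √(2 × 0.2249/1,800) = 1.58 points, so the shift is 1.67/1.58 = 1.05 standard errors, which gives 18.4%. For the 12-site test the noncentrality is 3,600 × (0.0167/2)² / 0.2249 = 1.11, which gives 8.4%.

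Pooling leaves the shift unchanged but narrows the half-width by √6. At one third, the shift is 22% of the half-width for two single sites (1.67/7.6) and 54% for 6 v 6 sites (1.67/3.1).

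**Range.**

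- Over f = 1% to 10% and R = 0 to 3, the shift runs from −0.5 to +1.0 points at 5% prevalence and from −3.3 to +6.7 points at one third.
- With f = 1% to 2% and R = 2, the shift is at most 0.7 points and the 12-site test rejects at most 5.5% of the time.
- At the extreme (one third, f = 10%, R = 3), the 12-site test rejects 81% of the time.
- If R = 1, or if every site has the same floor, the shift is zero.

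**The case against.** The other side has four good arguments.

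- **The choice is disclosed and justified.** Enrolling from 16 where permitted serves generalizability, and the limits come from outside the study. This stands; the point is not against enrolling these women.
- **An article is brief.** The exact comparison set and any age adjustment may be given in a full protocol or analysis plan that is not shown. The article does not say that the comparison uses every enrolled woman; that is only the plain reading. The stated aim of rates in a younger demographic may also imply a separate age-specific report. This limits how strongly the point can be put. It does not remove it, because the article itself fixes a site-dependent eligibility rule, the comparison across sites and jurisdictions, and the tests, and these interact.
- **The comparison is not a listed objective.** The primary and secondary objectives are proportions and patients' experiences. This stands and lowers the weight. However, the comparison is planned, and the per-site size of 300 is justified by having adequate power within each region or demographic.
- **The effect may be negligible.** With a small share of 16-17-year-olds it is, as the range shows.

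A reader might infer that part of any difference between sites reflects the age rule. The documents do not support that. It needs differing floors, which the article gives only as a possibility, and a different rate at ages 16-17, about which it says nothing. A gap of 10 to 30 percentage points is not supported either: at the 5% planning prevalence it would mean 15% to 35% in 16-17-year-olds, and a downward gap could not exceed 5 points.

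**Conclusion.** The concern holds in a limited form. The plan allows an age floor that can line up with jurisdiction and then compares jurisdictions without a common age range. Part of a difference between sites with different floors may therefore be an artefact of eligibility.

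The size cannot be known from the documents. On the mid assumptions it matters little for single-site contrasts. It could matter for contrasts pooled by jurisdiction if prevalence is near the pilot's level and floor and jurisdiction coincide. The 6 v 6 split used above assumes that they coincide fully.

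A reader might also infer that the primary estimate is compromised and that its population should be restricted to women 18 and over. That does not follow. The overall proportion moves little, and the article deliberately includes younger women for generalizability. What it needs is a statement that the lower age limit varies by site.

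**What to change.** In Data Analysis, state that comparisons of IPV prevalence across sites and jurisdictions use women aged 18 or older at every site. This makes the age-rule shift exactly zero. It does not remove differences in age mix among adults, which are a property of the clinics' populations and not of the eligibility rule.

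Report 16-17-year-olds as a separate descriptive group, with confidence intervals, from the sites that enrol them. This also serves the stated aim for the younger group.

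Keep the overall primary estimate on all enrolled women, and say beside it which sites used which floor.

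Make sure the questionnaire's age item can be split at 18. The bias section describes the demographic questions as categorical, so a band spanning 18 would prevent the split.

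The cost is a sentence or two and a filter on an item already collected. Enrolment and total sample size do not change. Sites with a floor of 16 lose a few women from the comparisons only: a 5% share leaves 0.95 × 300 = 285, and shares of 1% to 10% leave 297 to 270.
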